### Interventions

2.6

The interventions are compliant with the Consolidated Standards of Reporting Trials (27) and the Standards for Reporting Interventions in Clinical Trials of Acupuncture (28).

#### Verum acupuncture group

2.6.1

Patients allocated to the verum acupuncture group will receive treatment with needles inserted at the pre-specified acupuncture points. The acupoints include Baihui (GV20), Sishencong (EX-HN1), Shenting (GV24), Yintang (EX-HN3), Qihai (CV6), Guanyuan (CV4), bilateral Hegu (LI4), Shenmen (HT7), Zusanli (ST36), Fenglong (ST40), Xuanzhong (GB39), Taixi (KI3), and Taichong (LR3). Acupoint locations were determined according to the WHO Standard Acupuncture Point Locations in the Western Pacific Region (29) and are illustrated in Figure 2 and Table 2. The selection of these acupoints was based on clinical experience and previous experimental evidence. Prior clinical validation from our RCT (15) demonstrated cognitive improvement with the identical acupoint protocol. Manipulations including twirling, lifting, and thrusting will be performed on all needles for at least 30 min to reach De qi (a compositional sensation including soreness, numbness, distention, and heaviness), which is considered an essential component for acupuncture efficacy (30).

**Figure 2 fig2:**
[figure not shown]
Location of selected acupoints.

**Table 2 tab2:** Locations of acupoints.

Acupoints	Locations	Insert depth
Baihui (GV20)	On the head, 5 B-cun superior to the anterior hairline, on the anterior median line	0.5 ~ 0.8 cun
Sishencong (EX-HN1)	On the vertex, 1 cun from the front, back, left, and right to GV20, common 4 points	0.5 ~ 0.8 cun
Shenting (GV24)	On the head, 0.5 B-cun superior to the anterior hairline, on the anterior median line	0.5 ~ 0.8 cun
Yintang (EX-HN3)	At the forehead, at the midpoint between the two medial ends of the eyebrow	0.3 ~ 0.5 cun
Qihai (CV6)	On the lower abdomen, 1.5 B-cun inferior to the centre of the umbilicus, on the anterior median line	1 ~ 1.5 cun
Guanyuan (CV4)	On the lower abdomen, 3 B-cun inferior to the centre of the umbilicus, on the anterior median line	1 ~ 1.5 cun
Hegu (LI4) (bilateral)	On the dorsum of the hand, radial to the midpoint of the second metacarpal bone	0.5 ~ 1 cun
Shenmen (HT7) (bilateral)	On the anteromedial aspect of the wrist, radial to the flexor carpi ulnaris tendon, on the palmar wrist crease	0.3 ~ 0.5 cun
Zusanli (ST36) (bilateral)	On the anterior ascpect of the leg, on the line connecting ST35 with ST41, 3 B-cun inferior to ST35	1 ~ 2 cun
Fenglong (ST40) (bilateral)	On the anterolateral aspect of the leg, lateral border of the tibialis anterior muscle, 8 B-cun superior to the prominence the lateral malleolus	1 ~ 1.5 cun
Xuanzhong (GB39) (bilateral)	On the fibular aspect of the leg, anterior to the fibula, 3 B-cun proximal to the prominence of the lateral malleolus	0.5 ~ 0.8 cun
Taixi (KI3) (bilateral)	On the posteromedial aspect of the ankle, in the depression between the prominence of the medial malleolus and the calcaneal tendon	0.5 ~ 0.8 cun
Taichong (LR3) (bilateral)	On the dorsum of the foot, between the first and second metatarsal bones, in the depression distal to the junction of the bases of the two bones, over the dorsalis pedis artery	0.5 ~ 0.8 cun

* B-cun: proportional bone (skeletal) cun.

#### Sham acupuncture group

2.6.2

The acupuncturist will use a placebo needle in the sham acupuncture group. The placebo needle, whose tip is blunt, is designed so that participants will have a pinprick-like sensation when it touches the skin, while the needle will not penetrate the skin and appears to be inserted (Figure 3). The same acupoints as those in the verum acupuncture group are selected for placebo needle stimulation to avoid a site-specific effect of acupuncture.

**Figure 3 fig3:**
[figure not shown]
Park sham acupuncture device.

#### Waiting group

2.6.3

Patients in the WG will not receive acupuncture treatment during the observation period, and they will be provided 36 acupuncture sessions for free after observation.

#### Healthy group

2.6.4

The healthy participants will not receive any treatment.

### Clinical outcome measures

2.7

All patients will receive following scale assessment twice: in 12–24 h before the first acupuncture and in 24–72 h after the last acupuncture. Healthy volunteers will receive the assessment at baseline.

#### Primary outcomes

2.7.1

Episodic memory will be evaluated using the Auditory Verbal Learning Test-Huashan version (AVLT-H), which includes immediate recall (AVLT_N1-N3), 5 min delayed recall (AVLT_N4), 20 min delayed recall (AVLT_N5), cued recall (AVLT_N6), and recognition test (AVLT_N7). With a good reliability and validity in evaluating episodic memory of patients with aMCI (31), AVLT-H is used to assess the short-term delayed free recall and the long-term delayed free recall. The participant will be asked to learn and repeat a list of 12 words three times, with a short-delayed recall after an interval of 3–5 min, and a long-delayed recall, cue recall and identification after an interval of 20 min. The most sensitive evaluation index is the score of long-delay recall and identification. The higher the score, the better the memory function.

#### Secondary outcomes

2.7.2

The secondary outcomes include the following assessments: (1) Montreal Cognitive Assessment (MoCA), an accurate cognitive screening tool for use in general practice settings; (2) Mini-Mental State Examination (MMSE), a test used to assess overall cognitive function in patients with aMCI; (3) Hamilton Depression Scale (HAMD), a scale used to evaluate the emotional status of patients.

#### MRI outcomes

2.7.3

All patients will receive MRI scans twice: in 12–24 h before the first acupuncture and in 24–72 h after the last acupuncture. Healthy volunteers will undergo MRI scan at baseline. The 3D-T1 MRI scans will be conducted with a 3.0 T MRI scanner (Siemens MAGNETOM Prisma 3.0 T). The parameters for the T1 images for dataset 1 are as follows: repetition time (TR) = 2,200 ms, echo time (TE) = 2.45 ms, flip angle = 8°, field of view = 256 × 256 mm^2^, matrix size = 256 × 256, voxel size = 1 × 1 × 1 mm^3^, and slices = 175.

Resting-state functional MRI (rsfMRI) data will be collected within 7 min using the following parameters: epetition time = 2,000 ms, echo time = 30 ms, flip angle = 90°, field of view = 220 × 220 mm 2, matrix = 64 × 64, slice bb thickness = 3.2 mm, slice number = 37, and 240 volumes.

### Statistical analysis

2.8

Statistical analyses will be performed using SPSS software (Version 27.0, IBM Corp.), with a two-tailed *p*-value <0.05 being considered statistically significant. Normally distributed continuous variables will be expressed as mean ± standard deviation, with between-group comparisons being analyzed by independent samples t-test or one-way ANOVA (as appropriate), and within-group comparisons by paired t-test or repeated measures ANOVA. Non-normally distributed data will be presented as median (interquartile range) and analyzed using Wilcoxon rank-sum test. Categorical variables will be reported as frequencies (percentages), with between-group differences being assessed by chi-square test. In clinical between-group multiple comparisons, all *p*-values will be adjusted using the false discovery rate (FDR, Benjamini-Hochberg procedure) to control the risk of false-positive results (11).

Neuroimaging data will be processed using the DPABI V5.4 toolkit. Voxel-based morphometry (VBM) will be implemented to quantify volumetric characteristics of hippocampal subfields, while dynamic functional connectivity (aDC) analysis will be employed to characterize time-varying functional interactions between hippocampal subregions and other brain areas. Covariates including gender, age, educational attainment, and total intracranial volume will be regressed out during preprocessing. Statistical parametric maps will undergo Gaussian Random Field (GRF) correction for multiple comparisons at the cluster level. To detect voxel-wise alterations in hippocampal subfield functional connectivity (FC), mixed-effects models will be constructed to assess group differences, with interaction effects rigorously tested through permutation testing. All statistical outcomes will subsequently undergo False Discovery Rate (FDR) correction to control family-wise error across the entire analytical pipeline.

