### Study design

2.1

This is a prospective, single-center, three-armed, parallel-designed, assessor-blinded, randomized controlled trial. A total of 150 participants with aMCI and 50 healthy controls (HCs) will be enrolled. The 150 eligible patients will be randomly assigned to the verum acupuncture group, the sham acupuncture group, and the waiting group in a ratio of 1:1:1. Healthy volunteers will serve as a comparison group for baseline comparisons. The enrollment schedules, interventions, and assessments are summarized in Table 1. A study flowchart is provided in Figure 1.

**Table 1 tab1:** Schedule of enrollment, intervention, and assessments.

Item	Study period				
	aMCI				Healthy volunteers
	Baseline	Treatment phase			Baseline
	0 week	Week 1	→	Week 12	0 week
Enrollment					
Inclusion criteria	×				×
Exclusion criteria	×				×
Informed consent	×				×
Intervention					
Verum acupuncture group		×	×	×	
Sham acupuncture group		×	×	×	
Control group					
Outcome measurement					
Clinical features					
AVLT-H	×			×	×
MoCA	×			×	×
MMSE	×			×	×
HAMD-17	×			×	×
fMRI					
3DT1WI	×			×	×
T2WI	×			×	×
Flair	×			×	×
rs-fMRI	×			×	×
DTI	×			×	×
Safety					
Adverse events		×	×	×	

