### Sample size

2.2

The sample size for MRI studies is typically determined by practical constraints such as scanning time, cost, and effect size, so there is no unified standard. Desmond et al. conducted a statistical efficiency analysis based on the estimation of sample size in MRI studies, indicating that approximately 12 participants can achieve 80% power in typical activation at the voxel level (25). After considering that increasing the sample size could significantly enhance the stability of the results and accounting for a certain dropout rate, we therefore decided that each group will include 50 participants, totaling 150 aMCI patients and 50 healthy controls.

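### For non-normal data the plan names only the Wilcoxon rank-sum test, which is wrong for the before-after comparisons and leaves no overall three-arm or group-by-time analysis

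*Protocol article*

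**What the plan says.** All references are to the protocol article.

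- **Section 2.8 (Statistical analysis), normal data.** Between groups, the plan offers a t-test or one-way ANOVA, chosen as fits. It handles "within-group comparisons by paired t-test or repeated measures ANOVA". So it separates paired from unpaired data, and two groups from several.
- **Section 2.8, non-normal data.** One rule covers everything: "Non-normally distributed data will be presented as median (interquartile range) and analyzed using Wilcoxon rank-sum test". No signed-rank, Friedman or Kruskal-Wallis test appears anywhere in the article.
- **Section 2.8, multiplicity.** P-values from multiple between-group comparisons of clinical outcomes are adjusted by the Benjamini-Hochberg procedure.
- **Section 2.1 (Study design).** The study is a "three-armed, parallel-designed, assessor-blinded, randomized controlled trial". A healthy group is added for baseline comparison.
- **Section 2.2 (Sample size).** "each group will include 50 participants, totaling 150 aMCI patients and 50 healthy controls".
- **Section 2.7 (Clinical outcome measures).** "All patients will receive following scale assessment twice: in 12–24 h before the first acupuncture and in 24–72 h after the last acupuncture".
- **Abstract.** The intervention effect is to be explored by repeated-measures ANOVA, with no condition about normality attached.

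**The concern.** The rank-sum test assumes two independent samples. A patient's baseline and week-12 scores are not independent, so the test does not fit the before-after comparisons that the plan intends. Nor can one rank-sum test compare three arms, or four groups at baseline. And if an outcome fails a normality check, the plan does not say what replaces the repeated-measures ANOVA for the intervention effect.

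This is not a detail left to an unseen analysis plan. The article fixes the test itself, and drops for non-normal data the two distinctions it has just made for normal data.

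The branch could reach the primary outcome. Section 2.7.1 describes the AVLT-H task: "The participant will be asked to learn and repeat a list of 12 words three times". Each free-recall trial therefore yields an integer from 0 to 12, and section 2.4.1 selects patients whose AVLT_N5 lies more than 1 SD below the age-adjusted norm. At stake are the power and calibration of the before-after tests, and a clear rule for the three-arm comparison.

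**Working it through.** The plan states no figure that depends on this sentence, so there is nothing of its own to reproduce. The check asks what the rank-sum test does when it is applied as written.

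**Inputs from the article.** 50 patients per arm (section 2.2), two assessments per patient (section 2.7), three arms (section 2.1), two-sided alpha 0.05 and Benjamini-Hochberg adjustment (section 2.8).

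**Assumptions, not in the article.** Before-after correlation r from 0 to 0.8, and a true shift of 0.3 SD (normal data) or 0.4 SD on the log scale (skewed, log-normal data).

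**Step 1: type I error on paired data.** The rank-sum statistic uses a variance that assumes independence. With paired data its true variance is smaller by the factor 1 − ρ_S, where ρ_S is Spearman's correlation. For bivariate normal data ρ_S = (6/π)·arcsin(r/2), and the real size is about 2·[1 − Φ(1.96/√(1 − ρ_S))].

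- r = 0.5: ρ_S = 1.910 × 0.2527 = 0.483; 1.96/√0.517 = 2.73; size about 0.006.
- r = 0.7: ρ_S = 1.910 × 0.3576 = 0.683; 1.96/√0.317 = 3.48; size about 0.0005.

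Simulation agrees. With skewed data and 4,000 replicates, the rank-sum test rejected a true null in 0.042, 0.019, 0.006, 0.001 and 0.0003 of cases at r = 0, 0.3, 0.5, 0.7 and 0.8. The signed-rank test stayed between 0.044 and 0.053.

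**Step 2: power on paired data.** A paired test works with the standardised difference d/√(2(1 − r)). For d = 0.3 this is 0.21 at r = 0, 0.30 at r = 0.5 and 0.47 at r = 0.8. The rank-sum test gains nothing from the correlation. Simulated power with n = 50:

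| r | Rank-sum, 0.3 SD, normal | Signed-rank, 0.3 SD, normal | Rank-sum, 0.4 SD, skewed | Signed-rank, 0.4 SD, skewed |
|---|---|---|---|---|
| 0 | 0.30 | 0.31 | 0.49 | 0.46 |
| 0.3 | 0.28 | 0.40 | 0.49 | 0.60 |
| 0.5 | 0.24 | 0.53 | 0.48 | 0.74 |
| 0.7 | 0.20 | 0.73 | 0.49 | 0.92 |
| 0.8 | 0.16 | 0.89 | 0.49 | 0.99 |

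The two tests are about equal at r = 0, and the gap widens as the correlation rises.

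**Step 3: three arms with no true difference.** Rank-sum tests can be run for the three pairs of arms. With 50 per arm, the chance of at least one significant result was 0.110 unadjusted and 0.040 after Benjamini-Hochberg adjustment. A single Kruskal-Wallis test rejected in 0.045. The planned adjustment therefore controls false positives here. What is missing is a named overall test.

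**The case against.** The strongest reply is that the between-arm comparison, which is the one protected by randomisation, is largely sound. Pairwise rank-sum tests are valid for independent arms, and section 2.8 already adjusts them. This stands. A reader might infer that the plan cannot compare three arms, or that it inflates the family-wise error. The documents do not support either reading: the 0.110 in step 3 describes unadjusted testing, which is not what the plan prescribes.

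A second reply concerns baseline information. A reader might infer that a rank-sum analysis discards it. Section 2.8 does not say whether week-12 scores or changes would be ranked, and a rank-sum test on change scores would use the baseline. So a loss is possible but not established. The plan is silent on the point.

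Third, the Abstract's unconditional repeated-measures ANOVA may mean that the primary outcome never enters the non-normal branch. The article gives no AVLT-H distribution, and the outcome has several components, with no score range stated for them. That AVLT-H will be non-normal is plausible, not shown. But if the ANOVA is meant to hold regardless of normality, section 2.8 should say so, because its rule for non-normal data has no exception.

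Fourth, the paired error is conservative: it loses real changes and does not create false claims of benefit. That is right, and it limits the harm. It does not make the test correct.

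**Conclusion.** The point holds in a limited form. As written, section 2.8 prescribes an independent-samples test for paired data, names no overall test for three or more groups, and gives no counterpart to the Abstract's repeated-measures ANOVA when data are non-normal.

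The demonstrable harm falls on the within-group before-after tests. For correlations of 0.3 to 0.8 and a 0.3 SD shift, power is 0.28 falling to 0.16, where a signed-rank test has 0.40 rising to 0.89. The type I error drops from about 0.02 to almost nothing. These sizes rest on the assumed correlation and shift; the direction holds for any positive correlation. For the between-arm comparison the defect is one of specification, not of false-positive control. Whether the primary outcome is affected depends on its distribution, which the documents do not give.

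The sentence should be corrected, but it does not by itself undermine the randomised comparison.

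**What to change.** Replace the sentence on non-normal data in section 2.8 with a rule that mirrors the one for normal data:

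- Within-group before-after comparisons: Wilcoxon signed-rank test.
- Three or more groups: Kruskal-Wallis, followed by Benjamini-Hochberg-adjusted pairwise rank-sum tests. For the randomised comparison, apply this to change from baseline, or use rank ANCOVA on baseline, and state which.
- Rank-sum test: two independent groups only.

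Add a clause saying whether the repeated-measures ANOVA in the Abstract is kept or replaced when normality fails. The cost is one or two sentences of analysis text, with no change to data collection or sample size. It should be settled before the data are unblinded, so that the test is not chosen after the results are seen.

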#### Inclusion criteria

2.4.1

Patients of aMCI meet the following criteria: (1) diagnosis based on the aMCI diagnostic criteria proposed by Petersen (26); (2) right-handedness; (3) age 50–75 years without limitation of gender; (4) Objective Memory Impairment confirmed Auditory Verbal Learning Test Fifth Trial (AVLT_N5) score > 1 standard deviation (SD) below the age-adjusted normative mean; (5) self-reported memory impairment or cognition complaints by caregivers, with a disease course > 6 months.

Healthy controls meet the following criteria: (1) cognitive integrity confirmed by Mini-Mental State Examination (MMSE) score ≥27 and absence of subjective cognitive complaints; (2) right-handedness; (3) age 50–75 years without limitation of gender.

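### Regressing age, sex, education and intracranial volume out before the group test, as the article's wording implies, shrinks the non-randomised aMCI versus healthy-control imaging contrast

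*Protocol article*

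**What the plan says.** Section 2.8 of the protocol article puts covariate handling for the imaging data in the preparation stage: "Covariates including gender, age, educational attainment, and total intracranial volume will be regressed out during preprocessing". It then turns to inference. Statistical maps get a cluster-level correction, and for voxel-wise hippocampal connectivity "mixed-effects models will be constructed to assess group differences, with interaction effects rigorously tested through permutation testing". No covariate is named for that model or for the comparison of volumes.

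On who is compared, Sample size (2.2) states that "each group will include 50 participants, totaling 150 aMCI patients and 50 healthy controls". Under Study design (2.1) only the patients are "randomly assigned to the verum acupuncture group, the sham acupuncture group, and the waiting group in a ratio of 1:1:1", and "Healthy volunteers will serve as a comparison group for baseline comparisons". The Discussion places the patient-control comparison of hippocampal subregions first among the study's advantages. Both sets of inclusion criteria (2.4.1) specify "age 50–75 years without limitation of gender" and right-handedness. No matching on sex or education, and no age matching closer than that range, is stated.

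For clinical scores, section 2.8 plans t-tests or one-way ANOVA between groups, without covariates.

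**The concern.** Sex and education do not change within a person over the trial, intracranial volume is essentially fixed, and age moves by only 12 weeks. A regressor that is constant over one person's scan can remove nothing from that scan, so these four variables can be regressed out only across people. That is a group-level operation. If it is done first and groups are compared on what is left, any part of the group difference that runs parallel to a covariate is credited to the covariate and lost. The later test also does not know that degrees of freedom have been spent.

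Randomisation keeps the covariates nearly unrelated to arm, so little is lost between arms. Nothing does the same for patients against healthy volunteers. At stake is an understated and somewhat underpowered estimate of the baseline hippocampal differences in aMCI, the comparison meant to identify the pathological changes that acupuncture is then asked to reverse.

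**Working it through.** The article states no figure that depends on this rule, so there is none to reproduce. The check compares (a) one model holding group and covariates with (b) a pooled regression on the covariates, group left out, followed by a group contrast of the residuals.

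**Inputs from the article.** 150 patients and 50 controls (2.2); two-sided 5% level (2.8).

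**Assumptions, since the article gives none.** Size of the covariate imbalance; true adjusted difference 0.5 with residual SD 1; covariate slope 0.5 in the one-covariate case; a single outcome tested with a t-test, without the cluster or FDR corrections.

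**Identity.** Let G be group, X the covariates with intercept, and M the operator that takes residuals on X. The one-model estimate is G'My / G'MG. The two-step estimate divides the same numerator by the total sum of squares of G. Their ratio is G'MG / SS(G) = 1 - R2. It held in every simulated data set.

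**One covariate differing by d SD.** With p = 150/200 = 0.75, p(1-p) = 0.1875 and R2 = 0.1875d² / (1 + 0.1875d²).
- d = 0.5: 0.0469/1.0469 = 0.045. The estimate becomes 0.5 × 0.955 = 0.48.
- d = 1: 0.1875/1.1875 = 0.158. The estimate becomes 0.5 × 0.842 = 0.42.

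**Type I error.** Apart from degrees of freedom, the two-step statistic is the correct one times √(1 - R2). At d = 1, √0.842 = 0.918, so the effective cut-off is 1.96/0.918 = 2.136 and the two-sided rejection rate is 3.3%. At d = 0.5 the cut-off is 1.96/0.977 = 2.005 and the rate 4.5%.

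**Power.** At d = 1 the one-model non-centrality is 0.5 × √(200 × 0.1875 × 0.842) = 2.81, giving Φ(2.81 - 1.96) = 80%. The two-step test gives Φ(2.81 - 2.136) = 75%. Simulation (40,000 runs per setting) gave 79% and 74%. At d = 0.5 it gave 84% and 83%.

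**Four covariates** (4,000 runs per row). The stated SD imbalance applies to both age and education. The 0.5 and 0.8 rows add 10 percentage points on sex and 0.2 SD on intracranial volume.

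| Contrast | Imbalance | R2 | Two-step estimate (true 0.50) | Power, one model / two-step | Two-step type I error |
|---|---|---|---|---|---|
| 150 v 50 | none | 0.02 | 0.49 | 86% / 86% | 4.9% |
| 150 v 50 | 0.3 SD | 0.05 | 0.48 | 85% / 84% | 4.1% |
| 150 v 50 | 0.5 SD | 0.12 | 0.44 | 82% / 79% | 4.1% |
| 150 v 50 | 0.8 SD | 0.22 | 0.39 | 78% / 69% | 2.6% |
| one arm v controls, 50 v 50 | 0.5 SD | 0.16 | 0.42 | 62% / 55% | 4.0% |
| one arm v controls, 50 v 50 | 0.8 SD | 0.28 | 0.36 | 56% / 43% | 2.3% |
| two randomised arms, 50 v 50 | none | 0.04 | 0.48 | 69% / 69% | 5.5% |

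The one-model estimate was 0.50 throughout. The R2 values without imbalance are chance alone: 4/199 = 0.02 and 4/99 = 0.04.

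**Group-by-time between randomised arms** (2,000 runs). One common regression over both visits leaves the contrast unchanged (0.494 and 0.494). Separate regressions per visit give 0.476, a loss of about 4%.

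**The case against.** The strongest reply is that the decisive step is inferred. The article does not say that groups are tested on residuals from a regression omitting group, nor that covariates are barred from the later models, and a condensed article may leave a covariate list to a fuller document. That stands as a limit on certainty. If the covariate coefficients were estimated with group in the model, there would be no shrinkage. But the article does not leave the placement open: it assigns these variables to preprocessing. If group-level adjustment is meant, the sentence says something else and should be corrected anyway.

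Second, a reader might infer that the controls differ materially from the patients. The documents do not show this. They are silent on matching, the groups share an age range and handedness, and both are recruited from the same hospital. Silence on matching does not establish that R2 is large. At a 0.5 SD difference on one covariate the cost is about one point of power.

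Third, a reader might extend the criticism to the treatment effect. That is not supported either: between randomised arms the loss is about 4% or nil with unchanged power, and the AVLT-H analysis does not use this step. Nor does the rule produce false positive group differences, since its error is in the conservative direction.

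Finally, the unadjusted patient-control comparisons of clinical scores might be called confounded. Patients are selected on low AVLT recall and controls on a high MMSE, so those differences largely reflect selection. Adjusting them would bring consistency with the imaging analysis, but it is a side issue.

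**Conclusion.** The concern holds as a fault in a stated rule with limited reach. Followed as written, the sentence attenuates the baseline aMCI versus healthy-control imaging contrast relative to the covariate-adjusted one and makes its test conservative. The size depends on an imbalance that nobody can read from the article: a few per cent if the groups turn out similar, 16% for one covariate 1 SD apart, and 12-22% for all patients against controls if age and education both differ by 0.5-0.8 SD with the smaller sex and intracranial-volume differences (16-28% for one arm against controls). These figures assume a pooled regression without group and a simple t-test on one outcome. The randomised comparisons are barely touched and the primary outcome not at all. It is worth correcting because the affected comparison is one the authors rely on and the correction is nearly free.

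**What to change.** Replace the covariate sentence in section 2.8 with, for example: *Age, sex and education will be covariates in the same group-level model as group for hippocampal volume and connectivity, with total intracranial volume added for volume. Regression during preprocessing will be limited to within-scan nuisance signals.* Optionally, apply the same age, sex and education adjustment to the baseline patient-control comparisons of clinical scores.

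The cost is analysis wording only, with no new data. With four covariates and 200 people, residual degrees of freedom go from 198 to 194, and the two-step test was not entitled to those four in any case. The change is best made before any group results are seen.

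### Cluster-level random field correction does not assure family-wise control of the imaging maps if smoothness is uneven; the permutation testing named for connectivity interactions should cover all maps

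*Protocol article*

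**What the plan says.** The imaging paragraph of section 2.8 (Statistical analysis) describes two kinds of map. For structure, "Voxel-based morphometry (VBM) will be implemented to quantify volumetric characteristics of hippocampal subfields". For function, dynamic connectivity is meant to "characterize time-varying functional interactions between hippocampal subregions and other brain areas". It then sets one correction, with no map type exempted: "Statistical parametric maps will undergo Gaussian Random Field (GRF) correction for multiple comparisons at the cluster level".

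Permutation appears once, for hippocampal functional connectivity: "mixed-effects models will be constructed to assess group differences, with interaction effects rigorously tested through permutation testing". A last layer covers everything: "All statistical outcomes will subsequently undergo False Discovery Rate (FDR) correction to control family-wise error across the entire analytical pipeline".

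The only significance level is in the opening SPSS sentence of the section, "with a two-tailed *p*-value <0.05 being considered statistically significant". It is not tied to the GRF step.

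**The concern.** Cluster-extent GRF inference asks how large a chance cluster would be in a Gaussian field of a given smoothness. The standard form uses one global estimate. Where tissue is smoother than average, chance clusters are larger than the formula expects and pass the cut-off too easily. Where it is rougher, real clusters are penalised. Permutation does not need uniform smoothness to keep the overall error rate, yet the article names it only for connectivity interactions.

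The comparison most exposed is patients against healthy controls. Table 1 and section 2.7.3 give the controls a baseline scan only, so this comparison cannot be a group-by-time interaction, and nothing in the article moves it off GRF. The Discussion lists identifying pathological change in hippocampal subregions as a main advantage of the study. That is a claim about location, and this error depends on location. The later FDR layer does not repair it, because FDR takes the p-values it is given as valid.

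**Working it through.** **What the documents supply.** They give the method (cluster-level GRF), the general two-tailed 0.05, and the scope of permutation. They give no error rate, cluster-forming threshold, kernel, smoothness or search volume for the GRF step. There is therefore no figure of the plan to reproduce, and everything below is illustrative.

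**Assumed for the main illustration.** Null Gaussian fields on a 56×56×56 grid (V = 175,616 voxels); cluster-forming p of 0.001 or 0.01 one-sided (u = 3.09 or 2.33); 0.025 per tail, so 0.05 in total; 700 to 1,000 maps per setting. Smoothness is the full width at half maximum (FWHM) in voxels, either uniform or different in the two halves of the volume.

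**Formula.** P(largest cluster > k) = 1 − exp(−E[m]·exp(−β·k^(2/3))), with β = (Γ(5/2)·E[m]/E[N])^(2/3) and E[N] = V·(1 − Φ(u)). E[m] is the expected number of clusters, computed from the single global FWHM.

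**One setting worked through: FWHM 4 in one half, 6 in the other, u = 3.09.**

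1. The estimated global FWHM is 4.64, so the volume holds 175,616/4.64³ ≈ 1,758 resolution elements.
2. The main term of E[m] is 1,758 × (4 ln 2)^1.5/(2π)² × (u² − 1) × exp(−u²/2) ≈ 14.83. Surface and length terms add 2.01 and 0.08, so E[m] ≈ 16.92.
3. E[N] = 175,616 × 0.001 = 175.6, so β = (1.329 × 16.92/175.6)^(2/3) ≈ 0.254.
4. Setting P = 0.025 gives k = [ln(16.92/0.0253)/0.254]^(3/2) ≈ 130 voxels.
5. The simulated null 95th percentile of the largest cluster, both tails together, was 175 voxels. The cut-off of 130 is too small, and 11.8% of null maps exceeded it.

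**All half-and-half settings (nominal 5%; standard errors 0.7 to 1.9 points):**

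| FWHM in the two parts | p 0.001 | p 0.01 |
|---|---|---|
| uniform (4 or 5) | 3.1-3.7% | 4.0-4.1% |
| 4 and 5 (1.25-fold) | 6.4% | 10.1% |
| 4 and 6 (1.5-fold) | 11.8% | 21.5% |
| 4 and 8 (twofold) | 24.2% | 49.5% |
| 3 and 8 (2.67-fold) | 44.1% | 82.1% |

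In the uneven settings, 91% to 100% of the false-positive maps had their largest cluster in the smoother half.

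**Other layouts, to show how far the size depends on assumptions:**

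| Layout | Unevenness | p 0.001 | p 0.01 |
|---|---|---|---|
| part of the volume smoother | none | about 2% | about 2% |
| | 1.5-fold | 3-6% | 6-10% |
| | twofold | 13-15% | 22-26% |
| about 30% smoother, mildest results | none | 1-3% | 1-3% |
| | 1.5-fold | 5% | 5% |
| | twofold | 5% | 10% |
| | 2.25-fold | 10% | 21% |

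False clusters fell in the smoother part in 95-100% of cases in the first layout, and in 98% in the second at 2.25-fold.

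**Does permutation cure it?** A cut-off taken from the simulated null distribution of the largest cluster stands in for a maximum-cluster permutation test. The overall rate was 3.0% to 5.6% in the uneven half-and-half settings and 4% to 8% with 30% of the volume smoother, with 350 to 500 test maps each. At 350 maps the standard error around 5% is √(0.05 × 0.95/350) ≈ 1.2 points, and the cut-off is itself estimated, so this scatter is compatible with 5%. In the 30% layout, however, 96-100% of the false-positive maps still had their largest cluster in the smoother part. The overall rate is restored; the uneven location of errors is not.

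**The case against.** The strongest reply is that GRF is an established correction, that with near-uniform smoothness it holds or is conservative, and that the size of any excess comes from assumptions. Much of this stands. The layouts above differ about fivefold at twofold unevenness (5% and 10% against 24.2% and 49.5%). That volume and connectivity maps are unevenly smooth is general methods knowledge; the documents do not show it. If the volume analysis is confined to a hippocampal mask, smoothness may vary less there. Connectivity with other brain areas implies a wider search.

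Several stronger readings are tempting but unsupported. A reader might infer that a stated error rate is breached. None is stated for the GRF step, and only the general 0.05 can serve as the benchmark. A reader might fault the article for omitting threshold, kernel and mask. A condensed article commonly leaves these to the full protocol or analysis plan, where a smoothness adjustment may also sit, so their absence is no finding. A reader might take permutation as already planned for all maps. It is named for connectivity interactions only; if those are group-by-time effects, the connectivity tests closest to the treatment question already use it. Finally, a reader might expect maximum-cluster permutation to remove the dependence on local smoothness, and the simulation shows that it does not.

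What survives is that the article affirmatively chose GRF for its maps and confined permutation to one set of tests.

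**Conclusion.** The point holds in conditional form. If smoothness varies across the search volume, cluster-level GRF with one global smoothness and no adjustment does not assure family-wise control at 0.05 for the volume maps and for the patient-versus-healthy and group maps. Representative simulated rates are about 2% when smoothness is uniform, 3-10% at 1.5-fold and 13-26% at twofold; the mildest and harshest layouts lie outside those ranges. The direction and the concentration of false clusters in smoother tissue recur in every layout once unevenness is marked. The size rests on the assumed unevenness, smooth fraction and cluster-forming threshold.

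This is a worthwhile improvement, not a serious defect. It touches the mechanistic aim, which section 1 words as exploratory, and leaves the auditory-verbal learning test, the primary outcome, untouched.

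**What to change.** In section 2.8, replace GRF by permutation-based family-wise correction for all maps, using either the maximum cluster statistic or threshold-free cluster enhancement. Relabel whole participants and keep each patient's two scans together. If the maximum cluster statistic is used and conclusions about location are intended, add an adjustment of cluster size for local smoothness. Threshold-free enhancement was not simulated here, so its effect on where false clusters fall is not shown.

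The cost is a sentence or two and computing time, with no change to visits, scans or participants. Some borderline clusters may appear or vanish compared with GRF.
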